### Training of tobacco cessation counsellors delivering the intervention

Counsellors at UPHCs are allied healthcare workers and will be trained by the members of the research team to deliver counselling intervention. They will not be involved in data collection or data analysis. Their training will be done using a standardised training manual (hardcopy of study manual will be provided to these counsellors) to maintain the fidelity of the intervention.

#### Outcomes

The main outcomes expected from this exploratory trial include:

The proportion of all the tobacco users approached who consent to randomisation.The proportion of those randomised who comply with the intervention.The proportion of those randomised on whom follow-up data are collected at 3 months.

We will also assess the feasibility of assessing outcomes of primary interest in the main trial as listed below:

‘Self-reported tobacco abstinence’ of 7 days confirmed by a salivary cotinine test.Self-reported motivation and intention to quit.Cost-effectiveness as cost per disability-adjusted life year (DALY) averted.Cost-effectiveness as cost per quality-adjusted life year (QALY) gained.

The outcomes will be assessed at baseline on recruitment to the study and the end of 3 months. At baseline, sociodemographic details such as age, gender, educational level, marital status, religion, community, and economic status will be recorded. Variables related to tobacco consumption will be recorded, including the number of SLT products per day (frequency) consumed, age of initiation, number of previous cessation attempts and longest period of cessation. The data on quit attempts, the status of tobacco use and challenges will be recorded during baseline and end point. The biochemical validation of self-reported tobacco abstinence for 7 days will be assessed using salivary cotinine at the end of 3 months. The rapid test kit works through visual interpretation of colour developed on the kit and is instant in processing.^27 28^ Participants will be approached by the trial team members to provide a small sample of saliva, which will be collected through passive drooling. Collection, transportation and disposition of the biological samples and the kit will be managed at the study site by the site coordinator and research team. Cotinine is a preferred marker for tobacco use because cotinine stays in the body much longer than nicotine. The presence of cotinine in saliva or urine is a reliable indicator of tobacco use. Cotinine in vivo has a half-life of about 20 hours and lasts for about 3–4 days in the saliva and urine.^29 30^

#### Sample Size

Based on the primary outcomes in this exploratory trial of recruitment to the study and attrition, a total of 250 participants (125 participants per group) are required to estimate an anticipated proportion of 50% recruitment of participants with a 95% CI of 44% to 57% and 20% attrition at follow-up with a 95% CI of 15% to 25%. The sample size was calculated based on estimating proportions with a specified level of precision at the 95% level as measured by the width of the CI using the Sample Size Tables for Clinical Studies software.^31^

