**Methods and analysis:**

An exploratory randomised controlled trial will be conducted in urban primary health centres in the state of Odisha, India. A total of 250 smokeless tobacco users will be recruited to the study (125 in each arm). Participants in the intervention arm will receive routine care together with a face-to-face counselling intervention followed by advice and reminder mobile messages. The control arm will receive routine care, delivered by a primary care physician based on ‘Ask’ and ‘Advice’. All participants will be followed up for 3 months from the first counselling session. The primary outcome of this trial is to assess the feasibility to carry out a full randomised controlled trial.

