## Aim and objectives

Our overarching future aim is to evaluate within a randomised controlled trial, the clinical effectiveness (as measured by tobacco cessation) and cost-effectiveness of a complex intervention of face-to-face counselling coupled with mobile phone messaging delivered to SLT users visiting Indian primary care clinics in addition to routine care provided by the primary care professional against routine care alone. Prior to undertaking a full trial, we aim to develop and finalise the intervention and then test its acceptability and feasibility. Specific objectives of this study are to assess within an exploratory randomised controlled trial, the proportion of:

ll primary care SLT user attendees approached to take part in the trial that consent to randomisation.Those who are randomised to the intervention comply with the intervention.Those who are randomised on whom the follow-up data can be collected.Missing data on all research measures administered at baseline and 3 months, which will be used to assess the primary and secondary outcomes for conducting effectiveness randomised controlled trial in the future.

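### The recruitment precision in the sample-size statement is tied to the 250 randomised, who are the numerator of that proportion; with about 500 approached the 95% CI is about 46% to 54%, not 44% to 57%

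*Protocol article*

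**What the plan says.** The protocol article bases its sample size on the precision of two proportions, recruitment and attrition. Its Sample Size section states that 250 participants in two groups of 125 are "required to estimate an anticipated proportion of 50% recruitment of participants with a 95% CI of 44% to 57% and 20% attrition", and it gives 15% to 25% as the 95% CI for attrition. No number of people to be approached is given.

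The meaning of the 250 and of the recruitment proportion is set elsewhere:

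- **Outcomes**, first main outcome: "The proportion of all the tobacco users approached who consent to randomisation".
- **Aim and objectives** uses the same denominator: "primary care SLT user attendees approached to take part in the trial that consent to randomisation".
- **Abstract**, Methods and analysis: "A total of 250 smokeless tobacco users will be recruited to the study (125 in each arm".
- **Randomisation and allocation**: only eligible people who have already given informed consent are randomised.

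The compliance outcome is worded in two ways. Aim and objectives has "Those who are randomised to the intervention comply with the intervention", whereas Outcomes has "The proportion of those randomised who comply with the intervention".

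**The concern.** A consent proportion needs a count of people asked. The Sample Size section offers only a count of people who said yes and were allocated, and it attaches the recruitment interval to that count. The stated interval also fails a simple check: it runs 6 points below 50% and 7 points above, although the standard intervals are symmetric at exactly 50%.

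This is the only sample-size justification in the document, and feasibility is the trial's primary outcome. A reader who plans the approach log, or who tries to reproduce the precision, would take 250 as the number to approach when the design implies about twice that.

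**Working it through.** **Inputs.** 250 randomised, 125 per group (Sample Size; Abstract). Anticipated recruitment 50%, stated CI 44% to 57% (Sample Size). Anticipated attrition 20%, stated CI 15% to 25% (Sample Size). Recruitment denominator: those approached (Outcomes). Attrition denominator: those randomised, as the complement of the follow-up outcome (Outcomes).

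**Formula.** Wald 95% CI: p ± 1.96 × √(p(1 − p)/n).

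**1. Attrition as stated, p = 0.20, n = 250.** 1.96 × √(0.16/250) = 0.0496, so 15.04% to 24.96%. This rounds to 15% to 25% and reproduces the plan's figure.

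**2. Recruitment with 250 as denominator, p = 0.50.** 1.96 × √(0.25/250) = 0.0620. Results by method:

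| Method | 95% CI, n = 250 |
|---|---|
| Wald | 43.80% to 56.20% |
| Wilson, Agresti-Coull | 43.85% to 56.15% |
| Jeffreys | 43.83% to 56.17% |
| Clopper-Pearson | 43.63% to 56.37% |
| Wald, continuity-corrected | 43.60% to 56.40% |

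All round to 44% to 56%. None gives 57%.

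**3. What n would the stated width need?** The width is 13 points, so the half-width is 6.5. Then n = 1.96² × 0.25/0.065² = 227.3, or 228, which is neither 250 nor 500.

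**4. Recruitment with its defined denominator.** Number approached = 250/0.50 = 500. Then 1.96 × √(0.25/500) = 0.0438, so 45.6% to 54.4%. Clopper-Pearson gives 45.5% to 54.5%. The half-width is about 4.4 points, against 6.5 for the stated interval.

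**5. Could 250 be the number approached?** At 50% consent only 250 × 0.50 = 125 would be randomised in total, which contradicts 125 per group. Attrition of 20% on 125 would give 1.96 × √(0.16/125) = 0.0701, so 13.0% to 27.0%, which contradicts the stated 15% to 25%. This reading fails on both counts.

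The stated recruitment interval is therefore close to the n = 250 result and well away from the n = 500 result. That suggests 250 was used as the denominator, although the document does not say so in words.

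**The case against.** The best defence is that nothing in the trial depends on this interval. With about 500 approached, precision is better than claimed. The target of 250 stands on attrition alone: a half-width of 5 points at 20% needs 1.96² × 0.16/0.05² = 245.9, or 246. The Statistical analysis section will estimate the recruited proportion with a 95% CI from the data, so the planning figure enters no result. All of this stands, and it limits the severity.

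The 57% can also be defended as rounding or a typing slip. A proportion of 126/250 = 50.4%, shown as 50%, gives 44.2% to 56.6%, which rounds to 44% to 57%. This is possible, but a planning value of 50% is most naturally exactly 50%. The one-point miss is secondary to the denominator.

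A reader might go further on compliance, and the document does not support it:

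- **Compliance capped at 50%.** Read literally, the Outcomes wording counts all 250 in the denominator. But controls receive routine care alone (Interventions), and Aim and objectives names the intervention arm. Nothing plans to count controls as non-compliers, so only the wording needs to be brought into line.
- **Compliance left out of the sample size.** The section says its basis is recruitment and attrition. A precision calculation need not cover every main outcome.
- **No CI promised for compliance.** That can be left to the detailed analysis plan that the article announces.

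**Conclusion.** The point holds. The recruitment precision is wrong as written: the 250 are the consenters, the denominator should be about 500 approached, and the 95% CI should be about 46% to 54%. On the denominator apparently used, the upper limit is also one point too high.

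Severity is minor to moderate. A reader might infer that the trial is wrongly sized or that its sample-size justification collapses. It does not: the error understates precision, and 250 remains adequate for the stated attrition interval.

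The figure of 500 assumes that consent among those approached is the anticipated 50% and that everyone who consents is randomised. If either differs, the number approached and the interval change, but the 250 still cannot be the recruitment denominator.

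**What to change.** Restate the sentence in the Sample Size section along these lines: *With 250 randomised and an anticipated 50% consent, about 500 SLT users will be approached, which gives a 95% CI of about 46% to 54% for recruitment; 20% attrition among the 250 randomised gives a 95% CI of 15% to 25%.*

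Keep the denominator as people approached. Do not narrow it to eligible people, because neither list of outcomes does so and the change would alter the quantity being estimated.

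As a minor alignment, make the compliance denominator in the Outcomes section those randomised to the intervention, as in Aim and objectives.

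The cost is wording only, with no change to the number randomised, the design or the analysis.

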#### Randomisation and allocation

Randomisation will be done at the level of individual eligible participants who have provided informed consent. Randomisation will be stratified by study practice site (UPHCs) using random permuted blocks of varying block sizes from 4 to 10 and a 1:1 allocation to intervention or control arm. A randomisation list will be prepared by an independent statistician (from PRIMENT Clinical Trials Unit, University College London) not involved with this study. This list will be mailed to an independent staff member at the study site in India who will be responsible for the allocation of participants to the respective intervention arm. The independent staff member will assign a unique identification number to each of the consented participants and will maintain a list of those allocated to the respective study arm. The updated list will then be sent to the randomisation coordinator who will be responsible for overseeing the recruitment and randomisation process. The randomisation coordinator will remove all the participant identifiers from the list and finally send the list to the statistician for the purpose of analysis.

The trial will ensure a clear separation between staff who collect outcome data and those who deliver the intervention. Staff collecting outcome data will be blinded to the group assignment. None of the intervention staff, primary care physicians and behavioural counsellors will collect outcome data. All investigators, staff and participants will be kept masked to outcome measurements and any preliminary results emerging from the trial.

#### Data management

Baseline and end-point data will be collected from participants at UPHC using surveys in paper format. This will be entered electronically in the database developed in MS Access (Microsoft Office 2019). The quality of the data will be monitored by a data supervisor for completeness, validity and integrity. In case of incomplete data or inconsistent responses, the data supervisor will verify these with the study participants and update the entries in the database. The database will incorporate a range of inconsistency checks to limit data entry errors. Time-stamped audit trail will also be built in the database to independently record the date and time of operator entries and actions that create, modify, or delete electronic records.

### Data analysis

#### Statistical analysis

Participant characteristics will be summarised using mean and SD or median and IQR for continuous variables, and number and percentages for the categorical variables. The proportion of participants recruited and lost to follow-up at the end point will be estimated with 95% CIs. As part of the secondary analyses, logistic regression models will be used to estimate the intervention effects with 95% CIs for the prespecified outcomes, tobacco abstinence and self-reported motivation and intention to quit after adjusting for the stratification factor (UPHC) and baseline values of the outcome where it is available. These analyses will be done on an intention to treat (participants as randomised with available outcome data) basis, and multiple imputation will be used to handle missing outcome values if considered appropriate. The extent of missing data for each variable and the percentage of participants adhering to the intervention will be reported. Attrition levels by randomised group and the characteristics of participants who are lost to follow-up will also be reported. All analyses will be done using STATA software V.17 (StataCorp. 2019. *Stata Statistical Software: Release* V.17. College Station, Texas: StataCorp LLC) or updated versions. A detailed statistical analysis plan will be drawn up nearer to the analysis stage, prior to the database lock.

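### The analysis called intention to treat is an available-case, as-randomised analysis that would leave out about 50 of 250 participants at the anticipated attrition, with imputation only conditional

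*Protocol article*

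**What the plan says.** The Statistical analysis section of the protocol article places the effect estimates among the secondary analyses: "As part of the secondary analyses, logistic regression models will be used to estimate the intervention effects with 95% CIs". The outcomes are tobacco abstinence and self-reported motivation and intention to quit, adjusted for UPHC and, where available, the baseline value. The analysis set is then defined: "These analyses will be done on an intention to treat (participants as randomised with available outcome data) basis". The same sentence continues that "multiple imputation will be used to handle missing outcome values if considered appropriate". It gives no criterion for that judgement.

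The section also commits to reporting the extent of missing data for each variable, and adds: "Attrition levels by randomised group and the characteristics of participants who are lost to follow-up will also be reported". A detailed SAP is to be written before database lock.

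Three other places bear on the point:
- Outcomes defines the abstinence endpoint as a self-report "of 7 days confirmed by a salivary cotinine test". It states no rule for a participant who gives no sample.
- Sample Size anticipates "20% attrition at follow-up with a 95% CI of 15% to 25" per cent.
- Data management has end-point data collected at the UPHC, so a participant normally has to return to be counted.

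**The concern.** A reader who sees the term intention to treat will assume that all randomised participants are in the denominator. The text in brackets says otherwise: those without an outcome are outside the default set. By the plan's own figures that is one participant in five.

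Whether this matters depends on who is lost. Abstinence must be confirmed by a saliva test at a clinic visit, and it is plausible that continuing users are less willing to attend. If so, the rate among attenders is higher than the rate among all randomised. If loss also differs between arms, the comparison is distorted. Differential loss is plausible here, because only the intervention arm is sent messages three times a week for 3 months.

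At stake are the abstinence rates and the odds ratio that this trial will report. Outcomes lists confirmed abstinence among the outcomes of primary interest for the later full trial, so these estimates will probably be read closely even though they are secondary here.

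**Working it through.** **Inputs from the protocol article.** "a total of 250 participants (125 participants per group) are required" (Sample Size), "1:1 allocation to intervention or control arm" (Randomisation and allocation), and attrition of 20% with limits of 15% and 25% (Sample Size). The Introduction quotes earlier quit rates of 9% to 51.5%, which are 6-month figures and are used here only to show a range.

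**Assumptions, not in the documents.** A true abstinence rate *t* of 12%, abstinence *r* among those lost, and attrition that differs by arm.

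**1. The plan's attrition figure.** p ± 1.96 × √(p(1−p)/n) = 0.20 ± 1.96 × √(0.20 × 0.80/250) = 0.20 ± 0.0496, or 15.0% to 25.0%. The stated interval reproduces.

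**2. Participants left out.** 250 × 0.20 = 50, so about 200 are analysed, or 100 per arm if loss is equal.

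**3. Largest overstatement of a rate.** Let *q* be the rate among those seen and *m* the attrition. The rate among all randomised is q(1−m) + rm. It is lowest when r = 0, so *q* exceeds it by at most a factor of 1/(1−m):
- m = 15%: 1/0.85 = 1.18
- m = 20%: 1/0.80 = 1.25
- m = 25%: 1/0.75 = 1.33

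At 20% attrition, an available-case rate of 9% corresponds to at least 0.09 × 0.80 = 7.2% of all randomised, and 51.5% to at least 41.2%. With t = 12% and all dropouts using, the available-case rate is 0.12/0.80 = 15.0%.

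**4. Dependence on abstinence among those lost** (q = 20%, m = 20%):

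| r | Rate in all randomised | Error of available-case rate |
|---|---|---|
| 0% | 16% | +4 points |
| 10% | 18% | +2 points |
| 20% | 20% | 0 |
| 30% | 22% | −2 points |

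**5. Odds ratio with no true effect and all dropouts using.** Each arm's available-case odds are t/(1−m−t), so OR = (1−m_C−t)/(1−m_I−t), where I is intervention and C is control. With t = 12%:
- 20% v 20%: OR = 1
- 15% v 25% (I v C): 0.63/0.73 = 0.86; reversed, 1.16
- 10% v 30%: 0.58/0.78 = 0.74; reversed, 1.34

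At 15% v 25%, the OR is 0.66/0.76 = 0.87 for t = 9% and 0.235/0.335 = 0.70 for t = 51.5%.

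**6. The opposite rule under the opposite assumption.** Suppose t = 12% in both arms, loss is unrelated to abstinence, and attrition is 15% v 25%. Counting all missing as using gives 0.12 × 0.85 = 10.2% v 0.12 × 0.75 = 9.0%. OR = (0.102/0.898)/(0.090/0.910) ≈ 1.15. The available-case OR would be 1.

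**7. Scale against sampling error.** With 100 per arm and 15% abstinent, SE(log OR) = √(2 × (1/15 + 1/85)) = 0.40. The 95% CI around an OR of 1 is about 0.46 to 2.17.

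**The case against.** The strongest reply is that the plan does not simply discard non-returners. The sentence goes on to multiple imputation, attrition by arm and the characteristics of those lost will be reported, and Table 1 schedules a qualitative assessment of drop-outs. The imputation criterion, its variables and the sensitivity analyses are commonly left to an SAP, and one is promised. This is right as far as it goes, and their absence from the article is not the point. What remains is what the article does fix: the label and the default set. Reporting attrition reveals a problem but does not correct an estimate. Standard imputation assumes that data are missing at random, which is the assumption in doubt.

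A reader might also infer that abstinence rates will certainly be overstated. The documents do not support that. They say nothing about abstinence among those lost, and the one reason they give for poor attendance, in the Introduction, is loss of income from the journey rather than continued use. Steps 3 and 5 are worst cases. If those lost are as abstinent as those seen, the rate has no bias.

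Nor do the documents support making missing-as-using the sole main analysis. Step 6 shows that it can create a spurious effect about as large as the one it is meant to avoid. Calling a participant without a sample not confirmed is a reasonable convention, but Outcomes does not state it.

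Finally, it is tempting to say that an inflated control rate will set the full trial's sample size. Research impact says only that this study will inform a larger trial, so that use is an inference. The shifts at 15% v 25% with a 12% rate are also small beside the sampling error in step 7.

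**Conclusion.** The point holds as one of labelling and of a default analysis set that leaves the missing-data assumption untested. The set named intention to treat is available-case, as randomised. It omits about 50 of 250 participants at the anticipated attrition unless imputation is judged appropriate.

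The upper bound on overstatement of an abstinence rate is a factor of 1.25 at 20% attrition (1.18 to 1.33 across the stated interval). It is reached only if every dropout is still using. The odds ratio can move in either direction when attrition differs by arm. The figures of 0.86 and 1.16 rest on an assumed 12% rate in both arms, all dropouts using, and an assumed 15% v 25% split. Neither the size nor the sign of the actual bias can be known from the documents.

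Only secondary analyses are affected. The recruitment, compliance and follow-up proportions, which are this trial's main outcomes, do not depend on this set. The change is worth making but does not threaten the trial's purpose.

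**What to change.** In the protocol and the SAP:

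1. Name the present set available-case, as randomised, and drop the unqualified intention-to-treat label.
2. For cotinine-confirmed abstinence only, prespecify an analysis of all randomised participants, adjusted for UPHC, in which a missing self-report or missing saliva result counts as not confirmed abstinent. The convention does not carry over to motivation or intention to quit.
3. Report it beside the available-case analysis and a multiple imputation analysis that includes arm, UPHC and baseline use. Fix the imputation in advance instead of leaving it to later judgement.
4. Show the three sets of rates and odds ratios together with attrition by arm, so that dependence on the missing-data assumption is visible.

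The cost is a change of wording and two routine additional analyses, with no new data or participants. The drawback is that counting missing as not abstinent is itself an assumption and can bias the effect when attrition differs by arm, so it should not be the only analysis reported.
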